## 9.3 Time

The duration of infusion is generally not more than 1 hour. During the infusion process, the patients' vital signs and adverse reactions should be closely observed. If adverse symptoms occur, the infusion speed should be slowed down or the infusion should be stopped as appropriate.

## 9.4 Treatment Course

Infusions will be administered one time a week, a total of 4 times, and a course is 28 days.

# Management of Infusion Reactions

## 10.1 Delay/Pause/Stop Administration

If subjects experience any of the following adverse events, it is recommended to suspend or discontinue the administration of UC-MSCs to allow the subjects to recover from the toxicity, whether the adverse events are related to the administration or not.

- Criteria for discontinuation of administration are as follows:

1. If severe allergy occurs during the infusion process, such as anaphylactic shock, the administration should be stopped immediately and patients should be withdrawn from the trial;
2. If arterial or venous thrombosis occurs during the infusion process, such as deep vein thrombosis, myocardial infarction, etc., the investigator needs to judge the correlation with the infusion of UC-MSCs, and determines whether to continue the administration;

- Criteria for delay of administration are as follows:

1. Severe bleeding symptoms, such as gastrointestinal hemorrhage, and cerebral hemorrhage;
2. Febrile or infectious neutropenia;
3. Grade 3 or higher non-hematological toxicity, except in the following cases:

- Grade 3 nausea that can resolve with antiemetic treatment within 7 days
- Grade 3 vomiting that can resolve with antiemetic treatment within 7 days
- Grade 3 diarrhea that can resolve with antidiarrheal treatment within 7 days
- Grade 3 fatigue
- Grade 3 Weakness

If any of the above adverse effects occur, it is recommended to pause umbilical cord-derived MSC dosing until recovery to ≤ Grade 2 or baseline; Dosing should be restarted according to treatment schedule (Grade 2 laryngeal edema or Grade 2 bronchospasm requires full recovery).

In addition, if the platelet counts are ≥300×10^9^/L during the infusion, the drug administration can be suspended until the platelet counts are less than 300×10^9^/L, and then the administration can be resumed.

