# 5. Study Design and Statistical Methods

## 5.1 Study Design

This is a single-centre, open-label, single-arm study, which is divided into two-stage: dose-escalation stage, and dose-expansion stage.

In the dose-escalation stage, three successively increasing dose groups were set up, and the initial dose of the study was the lowest dose group. Subject enrollment, judgment and treatment of dose-limiting toxicity (DLT) refer to the traditional "3+3" dose-escalation design principle. That is, starting from the lowest dose group, 3 subjects were enrolled each time. If no DLT is observed, the trial will be continued at the next level dose; if DLT occurs in one of three patients, three more patients will be enrolled in the current dose, and when no DLT occurs anymore, the trial will be continued at the next level dose. If 2 or more DLTs occur in the 3 or 6 patients, the dose escalation will be stopped, and the current dose will be determined as the maximum tolerated dose (maximum tolerated dose, MTD). The flow of this trial is shown in Figure 1. Considering the safety of UC-MSCs, there will be 9 to 12 patients enrolled in the dose-escalation stage.

[figure not shown]
**Figure 1.** “3 + 3” dose-escalation protocol

[figure not shown]
The final dose in the dose-expansion phase will be determined based on the MTD in the dose-escalation phase, safety, efficacy, and opinion considered by the principal investigator, six patients will be enrolled in the dose-expansion stage to preliminarily explore the efficacy.

**Figure 2.** Six subjects will be enrolled to further evaluate the safety and efficacy of this dose infusion of umbilical cord MSCs

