**Definitions of Dose Limiting Toxicity (DLT)**

Newly appeared ≥ grade 3 adverse event that is related to UC-MSCs infusion occurred from the start of UC-MSC infusion to 1 month after the last infusion, and cannot be relieved to grade 1 within 72 hours after treatment with drugs or other interventions.

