# Usage, Dosage, Time and Course of Umbilical Cord-derived MSCs

## 9.1 Usage and Dosage of Umbilical Cord-derived MSCs

1. Name of cell products: Umbilical cord-derived MSCs.
2. Specification: 5mL/bag, the main component is MSCs derived from human umbilical cord cultured in vitro, containing 2.0×10^7^ cells. The cell cryopreservation solution is a compound electrolyte solution containing 5% human serum albumin and 10% dimethyl sulfoxide (DMSO).
3. Usage of cell products: Divide into 3 dose-escalation groups (Group A, Group B, and Group C) in turn, with 3 subjects in each group and proceed sequentially from low dose to high dose group according to the principle of dose-escalation. The specific number of subjects in the group is based on a traditional "3+3" dose-escalation protocol, 3 subjects will be enrolled each time, and if no DLT occurs in 3 cases, the trial will be continued at the next level dose; if DLT occurs in 1 of 3 patients, 3 more patients will be enrolled in the current dose, and when no DLT occurs anymore, the trial will be continued at the next level dose. If 2 or more DLTs occur in the 3 or 6 patients, the dose escalation will be stopped, and the current dose will be determined as the MTD.
4. 3 dose-escalation groups- Group A, Group B, and Group C:

- The dose of each infusion in Group A is 0.5×10^6^ cells/kg, intravenous infusion, once a week for a total of 4 times;
- The dose of each infusion in Group B is 1.0×10^6^ cells/kg, intravenous infusion, once a week for a total of 4 times;
- The dose of each infusion in Group C is 2.0×10^6^ cells/kg, intravenous infusion, once a week for a total of 4 times;

According to the above test results, the investigator will determine a specific dose experimental group (one of Group A, B, or C), and expand the sample size of the subjects to 6 cases.

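### Section 10.1 does not link a patient's own dosing to the DLT definition, so its restart rule allows a patient who met that definition to be re-dosed on schedule at the same dose

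*Protocol*

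**What the plan says.** **Toxicity threshold (Definitions of Dose Limiting Toxicity, after section 5.1).** A DLT is a new event of grade 3 or above, judged related, arising between the first infusion and one month after the last, which "cannot be relieved to grade 1 within 72 hours after treatment with drugs or other interventions".

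**Consequence of a DLT (Synopsis; sections 5.1 and 9.1).** The stated consequences concern the cohort or the trial: three more subjects, no further escalation, or stopping. With two or more DLTs, "the dose escalation will be stopped, and the current dose will be determined as the maximum tolerated dose". Nothing is said about the remaining infusions of the patient who had the event.

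**The patient's own dosing (section 10.1).** The section opens with a recommendation, whatever the causality: "it is recommended to suspend or discontinue the administration of UC-MSCs to allow the subjects to recover from the toxicity". One delay criterion is "Grade 3 or higher non-hematological toxicity, except in the following cases". The cases excepted are "Grade 3 fatigue" and grade 3 weakness, with no time limit, and grade 3 nausea, vomiting or diarrhea that can resolve with treatment within 7 days. After a delay, "it is recommended to pause umbilical cord-derived MSC dosing until recovery to ≤ Grade 2 or baseline; Dosing should be restarted according to treatment schedule". A stricter recovery standard applies to two events only: "Grade 2 laryngeal edema or Grade 2 bronchospasm requires full recovery".

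**Dose (section 9.1).** Each group has a single dose level, for example "The dose of each infusion in Group C is 2.0×10^6^ cells/kg, intravenous infusion, once a week for a total of 4 times". No reduced dose is described.

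**Mandatory stops.** These are severe allergy (10.1), a third Grade 3 infusion-related reaction (10.2.2) and a Grade 4 infusion-related reaction (10.2.3).

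**The concern.** The protocol uses two recovery standards for the same kind of event and does not connect them. One standard (grade 1 within 72 hours) decides whether an event counts against the dose. The other (Grade 2 or baseline, with no time limit) decides whether the patient goes on receiving that dose. The second is looser, and it is the only one that governs the individual patient.

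Safety is the primary objective. A toxicity serious enough to influence whether the next cohort may be treated has no stated consequence for the person who had it, although up to three infusions may still be due. The Compassionate use Regimen is stricter: it limits re-infusion to responders without obvious adverse reactions. Within the initial course, a patient with a DLT meets no comparable bar.

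**Working it through.** No sample-size or error-rate figure bears on this point. The check sets the rules side by side and then counts the exposure left.

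**1. Can one event satisfy both rules?** All events below are new and related. In the first three rows they are not relieved to grade 1 by 72 hours after treatment.

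| Event | DLT? | Section 10.1 |
| --- | --- | --- |
| Grade 3 rash, at grade 2 at 72 hours | Yes | Delay, but the restart condition is met at 72 hours |
| Grade 3 fatigue or weakness | Yes | No delay recommended |
| Grade 3 nausea, vomiting or diarrhea, resolving on days 4 to 7 of treatment | Yes | No delay recommended |
| Severe allergy, Grade 4 infusion reaction, third Grade 3 infusion reaction | Possible | Stop is mandatory (10.1, 10.2.3, 10.2.2) |

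The first three rows are the gap. Mandatory stops are set by type of event, not by DLT status, so they do not close it.

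**2. Does the timing allow it?** Infusions are weekly (section 9.4), so the planned gap is 7 days. The 72-hour clock is 3 days and starts at treatment of the event.

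- In the rash example, treatment on the infusion day means that the DLT is established on day 3, and the restart condition is also met on day 3. The next infusion is due on day 7.
- DLT status is known before the next infusion if treatment starts within 7 − 3 = 4 days of the previous one. If it starts later, the next infusion can fall due before the assessment is complete.
- If the ±2 day visit window in the flow chart also applies to infusions (an assumption), the gap from first to second infusion can be 7 − 2 = 5 days, and a later gap can be 7 − 2 − 2 = 3 days. Treatment would then have to start within 2 days, or on the infusion day itself.

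**3. How much exposure is left?** After a DLT following infusion k, 4 − k infusions remain: 3, 2, 1 or 0 for k = 1, 2, 3 or 4. The maximum is three infusions at the group dose (section 9.1):

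- Group A: 3 × 0.5 = 1.5×10^6 cells/kg
- Group B: 3 × 1.0 = 3.0×10^6 cells/kg
- Group C: 3 × 2.0 = 6.0×10^6 cells/kg

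That is at most three quarters of the planned course. A DLT first arising after infusion 4 leaves nothing to withhold.

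**4. How often?** The protocol gives no DLT rate, so this cannot be calculated from the document.

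**The case against.** **The investigator can stop.** This is the strongest reply, and much of it stands. Section 10.1 is worded as a recommendation and offers discontinuation as well as suspension. Section 13.1 allows withdrawal for adverse events, and section 13.4 provides for suspending the trial for a serious safety problem. Section 15.2 item 4 is a duty: after a serious adverse event the research unit must act at once to protect subjects. For non-hematological events outside the exceptions, the 10.1 trigger is also wider than the DLT definition, because relatedness is not required. These provisions soften the gap, mainly for serious events. None ties dosing to a DLT, and the only specific instruction on what follows a pause is to restart.

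**DLT is a cohort tool, and re-dosing after recovery is a legitimate choice.** It can be, particularly in refractory patients with few alternatives. But the protocol does not state that choice. It gives no recovery grade or dose for re-dosing after a DLT, and its general restart rule is looser than its own toxicity threshold.

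**Stronger readings that the document does not support.**

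- A reader might infer that the protocol requires re-dosing after a DLT. It does not, because discontinuation is open throughout.
- A reader might attach a probability, such as the chance of at least one DLT in 15 patients. Any rate would be invented, and the number is not fixed: DLT is judged in the escalation stage (9 to 12 patients), while total enrolment could be 9 + 6 = 15 to 12 + 6 = 18.
- A reader might extend the point to afebrile neutropenia, since the general delay criterion covers only non-hematological toxicity. That is literally right, but nothing in the protocol points to neutropenia as an expected effect, and the point does not need it.
- A reader might add patients who are mid-course when a dose meets the stopping rule. That is a separate, cohort-level question, partly covered by the Synopsis (stopping the trial) and by section 13.4.

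**Conclusion.** The point holds and should be fixed. Following section 10.1 as written, a patient who met the DLT definition can receive the next infusion on schedule at an unchanged dose, unless the event carries one of the three mandatory stops or someone uses a general power or duty to stop. The size is exposure, not demonstrated harm: at most three infusions, or 1.5, 3.0 or 6.0×10^6 cells/kg in groups A, B and C. The conclusion rests on the wording of the DLT definition and section 10.1 and on the fixed dose in section 9.1; it needs no assumed event rate.

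**What to change.** Add to section 10.1:

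*After a new, related event of grade 3 or higher, the next infusion is held until the 72-hour DLT assessment is complete. A patient who meets the DLT definition receives no further UC-MSC in this course; the grade 3 exceptions and the restart at Grade 2 or below do not apply to a DLT.*

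The hold is needed because, as the timing check shows, the next infusion can fall due before DLT status is known. Leave the within-infusion steps in 10.2.2 unchanged. They are taken during an infusion of generally no more than an hour, before a 72-hour criterion can be judged; the added rule governs later infusions.

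If the investigators prefer to allow re-dosing after a DLT, 10.1 should instead state the recovery grade and the dose for it.

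**Cost.** A short wording amendment, with no extra patients, visits or tests. If treatment of the event starts by the day the next infusion is due, waiting for the assessment delays that infusion by at most 3 days. A few patients may receive fewer than four infusions, and case-by-case re-dosing after a DLT is given up. Those patients stay in the Safety Set and Full Analysis Set (section 5.22) if they have the required later safety visit and efficacy evaluation.

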### 10.2.2 Grade 3 Infusion-related Reactions

If subjects experience a Grade 3 infusion-related reactions:

- - - The infusion should be stopped immediately.
    - Subjects should receive appropriate treatment with H1 receptor antagonists and/or paracetamol or prednisolone as clinically needed, with additional drugs added such as epinephrine and bronchodilators if needed.
    - Once symptoms are relieved, the infusion can be continued at an infusion rate not exceeding 50% of the initial rate until complete dosing. If Grade 3 symptoms recur, repeat the above steps. When the Grade 3 infusion-related reactions occur for the third time, subjects should terminate the infusion and should not receive further study drug treatment.

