### 10.2.3 Grade 4 Infusion-related Reactions

If subjects experience a Grade 4 infusion-related reaction:

- - - The infusion should be stopped immediately.
    - Subjects should receive appropriate treatment with H1 receptor antagonists and/or paracetamol or prednisolone (as clinically needed), with additional drugs added (e.g., epinephrine, bronchodilators) if needed.
    - Subjects should no longer receive study drug treatment.

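### Sections 10.1 and 10.2.3 give incompatible instructions for a Grade 4 infusion reaction that is not a severe allergy or thrombosis, and no precedence is stated

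*Protocol*

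**What the plan says.** Both rules stand in the protocol chapter on managing infusion reactions.

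**Section 10.1** recommends suspending or discontinuing administration for listed events, "whether the adverse events are related to the administration or not". It then splits the events into two lists.

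- *Discontinuation.* For severe allergy during the infusion, with anaphylactic shock as the example and no grade given, "the administration should be stopped immediately and patients should be withdrawn from the trial". For arterial or venous thrombosis, the investigator judges relatedness and decides whether to go on.
- *Delay.* One criterion is "Grade 3 or higher non-hematological toxicity, except in the following cases". The five exceptions are Grade 3 nausea, vomiting and diarrhea (each if it resolves with treatment within 7 days), Grade 3 fatigue and Grade 3 weakness. For events on this list "it is recommended to pause umbilical cord-derived MSC dosing until recovery to ≤ Grade 2 or baseline", and then "Dosing should be restarted according to treatment schedule". A note adds a stricter recovery requirement for Grade 2 laryngeal edema and Grade 2 bronchospasm.

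**Section 10.2** gives a CTCAE grade table for infusion-related reactions and a rule by grade.

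- *10.2.2, Grade 3.* The infusion is stopped and the subject treated. "Once symptoms are relieved, the infusion can be continued at an infusion rate not exceeding 50% of the initial rate until complete dosing". At the third occurrence, study treatment ends.
- *10.2.3, Grade 4.* The infusion is stopped and the subject treated. "Subjects should no longer receive study drug treatment".

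No sentence in section 10 says which part prevails when both cover the same event.

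**The concern.** A Grade 4 infusion-related reaction is a non-hematological toxicity of Grade 3 or higher in almost any form it could take, so it appears to meet the 10.1 delay criterion and the 10.2.3 rule at once. One leads to a restart after recovery and the other to no further treatment.

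First, this is a matter of patient safety: staff handling a life-threatening reaction would have to work out for themselves which instruction applies. It is also a matter of interpretation. The primary endpoint is safety, escalation proceeds in cohorts of three, and the number of infusions a subject receives is the exposure behind that subject's safety record. If two subjects with the same reaction can be handled differently, with both within the protocol, their exposure and length of DLT observation differ for a reason that the plan does not control.

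**Working it through.** The plan gives no figure to reproduce. The check sets the rules side by side and then counts infusions and weeks.

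**Step 1. Does 10.1 reach infusion reactions?** Yes, on its wording. It sits under the infusion-reaction chapter heading, applies regardless of relatedness, and does not list infusion reactions among its five exceptions. Its recovery note names laryngeal edema and bronchospasm, which suggests that reactions of this kind were in view.

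**Step 2. Compare the rules by type of event.**

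| Event during infusion | 10.1 | 10.2 | Compatible? |
|---|---|---|---|
| Grade 4, severe allergy | Stop, withdraw | No further treatment (10.2.3) | Yes, on ending treatment |
| Grade 4, thrombosis | Investigator decides | No further treatment, if classed as an infusion reaction | Set aside: 10.1 fixes no rule of its own |
| Grade 4, any other | Pause, then restart on schedule | No further treatment (10.2.3) | **No** |
| Grade 3, judged a severe allergy | Stop, withdraw | Infusion can continue (10.2.2) | **No, if both are held to apply** |
| Grade 3, any other | Pause to Grade 2 or lower or baseline, then restart on schedule | Stop; can continue at half the initial rate or less; end at third occurrence | Largely yes |

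The fourth row arises because 10.1 gives no grade for severe allergy, while the definition under the grade table covers adverse reactions to infused biological substances in general. In addition, 10.2.2 itself provides for epinephrine and bronchodilators. A Grade 3 allergic reaction can therefore be read into either section.

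In the fifth row, stopping until symptoms are relieved fits with pausing until recovery. The rate limit and the recurrence cap add to 10.1 and do not negate it.

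**Step 3. Infusions at stake in the third row.** Inputs: 4 weekly infusions (section 9.4), given at D1, W1, W2 and W3 in the attached flow chart. If the reaction occurs at infusion *k*, 10.2.3 allows 0 further infusions and 10.1 allows up to 4 − *k*.

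| Reaction at infusion | Further infusions, 10.2.3 | Further infusions, 10.1 (maximum) | Difference as share of 4 |
|---|---|---|---|
| 1 | 0 | 4 − 1 = 3 | 3/4 = 75% |
| 2 | 0 | 4 − 2 = 2 | 2/4 = 50% |
| 3 | 0 | 4 − 3 = 1 | 1/4 = 25% |
| 4 | 0 | 4 − 4 = 0 | 0% |

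**Step 4. DLT window.** Under the DLT definition in section 5.1, the window closes 1 month after the last infusion. For a reaction at infusion 1, the last infusion is at D1 under 10.2.3 and at W3 under 10.1 if no dose is delayed. The end of the window then differs by 3 − 0 = 3 weeks, and by more if the pause shifts later doses.

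**Step 5. DLT status of the reaction itself.** The definition depends on the event being new, on grade, on relatedness and on relief to Grade 1 within 72 hours. None of these depends on which section governs re-dosing.

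**The case against.** The strongest reply is that a specific rule overrides a general one. Section 10.2 is devoted to infusion-related reactions, carries its own grade table and has a rule for every grade from 1 to 4. Section 10.1 is a general list that also covers bleeding and neutropenia. Many readers would simply apply 10.2. That reading is plausible, but the protocol does not state it, and the mention of laryngeal edema and bronchospasm in 10.1 cuts against it.

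A second reply is that the opening of 10.1 allows suspension or discontinuation, so ending treatment is within its terms. Section 13.1 also lets the investigator withdraw a subject who is unsuitable to continue after an adverse event. Both permit stopping. Neither removes the conflict, because 10.1 puts Grade 3 or higher toxicity on the delay list and follows that list with an instruction to restart. Only the pause is worded as a recommendation; the restart uses the same verb as 10.2.3.

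Other limits stand in full, and they rule out stronger readings that a reader might infer:

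- *That the Grade 3 rules contradict each other throughout.* They do not. 10.1 recommends and 10.2.2 permits, so a clinician can mostly satisfy both. Only the ungraded allergy criterion clashes.
- *That every Grade 4 reaction is affected.* Severe allergy ends treatment under both sections.
- *That a third of the data for an escalation decision is at stake.* One subject is 1 of 3 in an initial cohort, but that subject's reaction is judged for DLT in the same way under either section, and the subject's place in the safety set does not depend on the choice. What changes is the chance of observing a later DLT, which matters chiefly when the first event was not one.
- *That the efficacy analysis is materially affected through per-protocol status.* Section 5.22 gives that set only an auxiliary role.

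**Conclusion.** The point holds in a narrow form. For a Grade 4 infusion-related reaction that is neither a severe allergy nor a thrombosis, restarting under 10.1 and ending treatment under 10.2.3 cannot both apply, and precedence is unstated. A second, smaller overlap exists for a Grade 3 reaction that is judged a severe allergy.

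The size is bounded by one extreme case: up to 3 of 4 infusions (75%) or none, with the end of the DLT window moving by about three weeks. This assumes a reaction at the first infusion, recovery in time to keep the schedule, and a reader who applies 10.1 over 10.2.3. For later reactions the difference shrinks, to zero infusions at the fourth. The protocol gives no basis for estimating how often such a reaction would occur, so no expected effect on the results can be stated.

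This is a patient-facing contradiction that should be corrected. It does not undermine the design, the sample size or the DLT definition.

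**What to change.** Reconcile 10.1 with 10.2.2 and 10.2.3 so that each grade of infusion reaction has a single rule. Say in one sentence which section governs when an event meets both. Treat severe allergy in the same way: state how it relates to the grades in the 10.2 table, so that a given reaction leads to one rule only. Which rule applies to which grade is a clinical decision for the investigator and sponsor.

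The cost is a wording amendment to section 10 with ethics approval. It changes no sample size, visit or analysis. If subjects were treated before the amendment, the report can state how any Grade 3 or 4 infusion reaction was handled and how many infusions followed. Section 15.2 already requires treatment measures for adverse events to be entered in the CRF.
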